## Secondary Outcome

We will observe changes in the ANS after active and sham tDCS combined with VR tasks in children and adolescents with CP.

### Assessments for Secondary Outcome

In addition to the motor tests, the HRV analysis will be verified throughout the intervention. Some studies point to ANS alteration, with a reduction in HRV in individuals with CP (77, 78). HRV represents the autonomic function, and short-term HRV measurement has been used to evaluate sympathetic and parasympathetic heart rate modulation. Therefore, because of the ease of evaluation (non-invasively, through a chest strip) and because of its high clinical relevance, it is important to evaluate HRV before and during the intervention with tDCS and VR, since some studies indicate improvement of the autonomic balance after VR tasks in individuals with Duchenne muscular dystrophy (72) and post-stroke (79). In the case of CP, some studies had identified low HRV in foetuses that would later be given a CP diagnosis (80), at rest and during postural change (81), and submaximal tests (78). Low HRV is often an indicator of abnormal and insufficient ANS adaptation, which may indicate the presence of physiological malfunction in the individual (50) and is associated with an increased risk of cardiac events (6).

## Statistical Analysis

For the coincident timing task for the inferential analysis of the initial tasks (transversal) and the longitudinal protocol with tDCS and HRV as dependent variables, the error measures (constant, absolute, and variable errors) will be considered (time in milliseconds). If the data meet the assumptions for the use of parametric analysis, ANOVA will be performed to identify intra and inter-group differences. These, if any, will be detected by the *post hoc* Tukey-HSD test. If the normality assumptions are not met, non-parametric analyses will be undertaken to identify and locate the differences: a Friedman and *post hoc* Wilcoxon test (for within groups) and a Kruskal–Wallis and *post hoc* Mann–Whitney *U*-test (between groups). For the between-groups analysis of HRV indices, MANOVA will be used, with repeated measures for within groups analyses (for evaluations and follow-up) or Mann–Whitney for intergroup analyses and Friedman for intragroup analyses. A significance level of 0.05 (5%) will be defined; all intervals constructed throughout the work will be 95% statistical confidence. The statistical program used will be SPSS (Statistical Package for Social Sciences), version 26.0.

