### Overview of the Study Design

A triple-blinded randomised controlled crossover trial with a 1:1 allocation ratio will be conducted, and all participants will undertake non-immersive VR tasks and active or sham tDCS. Groups A–S will start with 10 daily sessions of tDCS-active combined with VR tasks for 20 min. After a 1 month washout, this group will be reallocated to another 10 daily sessions of 20 min with sham tDCS combined with VR tasks. Meanwhile, groups S–A will carry out the opposite protocol (participants will start an allocated 10 sessions of sham tDCS combined with VR tasks, and after a 1 month washout period will be reallocated to 10 sessions of active tDCS combined with VR tasks). The 1 month washout period has been used and was shown to be sufficient to reset the effects of the first 10 sessions in Biabani et al. (31). Figure 2 summarises the planned experimental design. This research protocol follows the SPIRIT recommendations.

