### Randomisation

Participants will be randomly allocated to either group A-S (active tDCS and VR tasks) or group S-A (sham tDCS and VR tasks) with a 1:1 allocation defined by a website (randomization.com). As we will have the participant's characteristics, immediately after the randomisation the age and motor function (GMFCS/MACS) will be compared between groups; if the groups are not homogeneous, a new randomisation will be carried out. This protocol will be repeated until there is no difference between age and GMFCS amongst groups (in a maximum of first three attempts at randomisation, we always have homogeneous groups). Randomisation will be under the control of a blinded investigator who will be the only person allowed to manage the electronic security file of the randomisation to locate the individuals. (More details about this can be found in the section that follows). The investigator will be blind to the group to which the participant is allocated.

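### The named tests do not fit the two-sequence crossover: no active-versus-sham contrast and no period term is stated, so the main hypothesis has no matching test

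*Protocol article*

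**What the plan says.** The Overview of the Study Design states the design: "A triple-blinded randomised controlled crossover trial with a 1:1 allocation ratio will be conducted". Of the group that starts on active stimulation it says: "After a 1 month washout, this group will be reallocated to another 10 daily sessions of 20 min with sham tDCS combined with VR tasks". The other group follows the reverse order. The Randomisation section labels the two groups A-S and S-A, so a randomised group is a sequence and every child receives both conditions.

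The Statistical Analysis section describes the tests in terms of groups. For the timing errors: "If the data meet the assumptions for the use of parametric analysis, ANOVA will be performed to identify intra and inter-group differences", with Tukey-HSD afterwards. If normality fails, Friedman with Wilcoxon is used within groups and Kruskal–Wallis with Mann–Whitney between groups. For heart rate variability (HRV) it plans MANOVA between groups with repeated measures within groups, "or Mann–Whitney for intergroup analyses and Friedman for intragroup analyses". The section names no contrast of active with sham, no period factor, and no test that joins the two periods.

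The Introduction gives the hypothesis. All children are expected to improve with VR practice and to retain the gain at 30 days, and the benefit is expected to be larger after active than after sham stimulation.

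**The concern.** The question is whether active stimulation adds to VR practice. In a crossover, each child's active period is compared with the same child's sham period, after allowing for the order in which they came. The named tests are those of a parallel-group trial with repeated visits. Followed as written, they test something other than treatment, test treatment with the wrong error term, or mix treatment with period.

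The period matters here because the authors expect practice gains in everyone, still present at 30 days, which is about the length of the washout. At stake are the power that the crossover design should provide and whether a null between-group result says anything about tDCS.

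**Working it through.** **Inputs.** From the article: 28 children before dropout (14 per sequence), d = 0.65, alpha 0.05 (taken as two-sided). Assumed, because the article gives neither: within-person correlation ρ between periods of 0, 0.3, 0.5 or 0.7, and a period (practice) effect π of 0, 0.65 or 1 SD. One outcome per period, total SD 1, treatment effect τ, no carry-over. How 28 was derived is a separate matter; it is used here only as the sample size.

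**Expected values.** Setting the sham period-1 mean to 0:

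| Sequence | Period 1 | Period 2 |
|---|---|---|
| A-S | τ | π |
| S-A | 0 | τ + π |

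**1. Group = sequence, both periods.** The A-S mean is (τ + π)/2 and the S-A mean is (0 + τ + π)/2. The difference is 0 whatever τ is. In simulation with τ = 0.65 this comparison rejects about 5% of the time at every correlation and period effect tried.

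**2. Group = sequence, period 1 only.** The difference is τ, so this is a valid comparison, but it uses half the data. Power of a two-sample t-test with 14 per group at d = 0.65 is 0.38.

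**3. Within one sequence, active minus sham.** A-S gives τ − π and S-A gives (τ + π) − 0 = τ + π. With τ = π = 0.65 these are 0 and 1.30. Neither isolates τ. Finding significance in one sequence and not in the other is not a test of treatment.

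**4. Group = condition, 28 active values against 28 sham values.** The contrast targets τ, but each child appears on both sides. The true variance of the difference in means is 2(1 − ρ)/28, whereas an unpaired test assumes 2/28. At ρ = 0.5 these are 0.036 and 0.071, so the test uses twice the true variance.

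**5. Crossover test.** Compare within-child period differences between the sequences. With d_z = 0.65/√(2(1 − ρ)), the noncentrality is d_z·√28 on 26 degrees of freedom. At ρ = 0.5, d_z = 0.65 and the noncentrality is 0.65 × 5.29 = 3.44, giving power 0.91. A period effect cancels from this comparison.

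With no period effect (Mann–Whitney by simulation; repeat runs differ by up to about 0.03 in power):

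| ρ (assumed) | Mann–Whitney null rejection | Mann–Whitney power | Crossover power |
|---|---|---|---|
| 0 | about 0.05 | about 0.65 | 0.65 |
| 0.3 | about 0.02 | about 0.67 | 0.80 |
| 0.5 | about 0.006 | about 0.68 | 0.91 |
| 0.7 | about 0.002 | about 0.72 | 0.99 |

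With an assumed 1 SD period effect, Mann–Whitney power falls to about 0.55, while the crossover test is unchanged. A paired t-test without a period term, under a 0.65 SD period effect, has power 0.71, 0.83 and 0.95 at ρ = 0.3, 0.5 and 0.7, against 0.80, 0.91 and 0.99.

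**6. Unequal sequences.** If n₁ children complete A-S and n₂ complete S-A, the pooled active-minus-sham mean without a period term is τ + π(n₂ − n₁)/(n₁ + n₂). With equal numbers the bias is zero. With, say, 12 and 16 completers it is π × 4/28 = 0.14π.

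**The case against.** Three objections have weight.

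First, some of the plan does use the pairing. Friedman, Wilcoxon and the HRV repeated measures all work on the same child repeatedly. A reader might infer that the plan ignores the participant altogether; the text does not support that. The difficulty is that these tests are placed within groups, where step 3 applies.

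Second, the ANOVA has no factor list. Looking for differences both within and between groups could describe a mixed ANOVA whose group-by-period interaction carries the treatment effect. A reader might infer that the parametric route cannot estimate active versus sham; that also goes too far. What can be said is that no such interaction or contrast is stated. An article may leave factor lists to a fuller document, but this one commits to Kruskal–Wallis and Mann–Whitney between groups, which do not suit paired crossover data.

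Third, the size depends on assumptions. At zero correlation and no period effect there is almost no loss. The Primary Outcome section defines the outcome as change from baseline. If each period has its own D0, retained practice gains would largely drop out of the change, and the correlation between the two changes may be below 0.5. Both would shrink the losses shown.

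A reader might also infer a risk of false positive claims. For the pooled active-versus-sham tests the error runs the other way: with equal sequences they reject too rarely under the null.

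**Conclusion.** The point holds. The Statistical Analysis section names tests that do not match the design in the Overview and Randomisation sections, and the main hypothesis has no stated test that separates treatment from period and uses each child as its own control. This is more than missing detail, because specific unsuitable tests are named.

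On the active-versus-sham reading, the power loss at 14 + 14 and d = 0.65 with no period effect runs from about nil at correlation 0 to about 0.27 (0.99 − 0.72) at 0.7, and is larger with a practice effect. On the sequence reading over both periods, the test has no power for treatment at all. Bias arises only if the sequences finish unequal and a period effect exists. The correlations and period effects are illustrative. The cancellation in step 1 and the confounding in step 3 do not depend on their values, except that the confounding vanishes if there is no period effect.

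**What to change.** For the treatment question, replace the between-group and within-group scheme with a crossover analysis:

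- Outcome: each period's D11 value, or the change from that period's D0.
- Model: treatment, period and sequence as fixed effects, participant as random effect.
- Equally acceptable: a two-sample t-test of within-participant period differences between the sequences, or its rank version if the data are clearly non-normal.
- Report the active-minus-sham estimate with its 95% CI.
- Apply the same analysis to each HRV index.
- Say in the text whether group means sequence or condition wherever the word is used.

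The cost is a rewrite of the statistical section. No new data are needed, and the analysis runs in the planned SPSS 26.

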**Figure 2 F2:**
[figure not shown]
Study design. MACS, Manual Ability Classification System; GMFCS, Gross Motor Function Classification System; PEDI, Pediatric Evaluation of Disability Inventory; VR, virtual reality; n: sample size; tDCS, transcranial direct current stimulation; D0-D11, days of interventions in which D0 is the baseline, D1 to D10 are the days of interventions and the D11 is the day of the final assessments. Participants and sampling.

Thirty-six participants will be recruited through referral by the coordinators of three clinics in Brazil: *Intensiva, Intertherapy*, and *Therapies*, located in São Paulo state. Those interested in participating will undergo a detailed screening using the eligibility criteria for enrolment in the study.

The sample size was calculated using statistical software (GPower 3.1.5) on the main outcome measure (i.e., the motor score). This calculation was based on data from one study with a group of individuals with CP who received tDCS (32). The power was 0.80; the alpha was 0.05; and the effect size was 0.65 (Cohen's d). The sample estimation indicated that 28 participants would be necessary (i.e., 14 per group). With an adjustment to allow for a withdrawal rate (20%), we will recruit 36 participants.

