## Assessment Protocol

The assessment protocol will have the following sequence: the assessment scales will be undertaken with the participants' parents in a separate room (PEDI, Abilhand-Kids, and *ACTIVLIM-CP*), and GMFCS and MACS will be carried out by observacional analysis of their abilities. Also, cognitive (WISC-IV) and visual assessments (*Titmus Test and Ishihara Test)* will be made by a psychologist and a psychometrist, respectively.

Then, for the VR assessment, the coincident timing task will be carried out with a short-term motor learning protocol as used by Monteiro et al. (17), with 20 repetitions for acquisition. After 15 min of no contact with the task, the participants will perform five repetitions of the same task (for retention analysis), and five more repetitions with a speed increase (for transfer of performance analysis).

The reaction time task will be carried out with two attempts of adaptation and 10 attempts for analysis, as used by Crocetta et al. (71).

The HRV will be assessed by 20 min of rest seated in a comfortable chair or their own wheelchair, as used by Alvarez et al. (72).

The assessment part of the protocol will take around 1 h and 30 min in total (inferential analysis method follows in the item “Data analysis”).

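### The timing-error analysis is chosen by how the outcome data look, and the rank fallback as named does not use the within-child active-minus-sham contrast of the crossover.

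*Protocol article*

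**What the plan says.** The Statistical Analysis section names three outcome measures for the coincident timing task: "the error measures (constant, absolute, and variable errors) will be considered (time in milliseconds"). The method then depends on a check: "If the data meet the assumptions for the use of parametric analysis, ANOVA will be performed to identify intra and inter-group differences", with Tukey-HSD afterwards. The alternative is "If the normality assumptions are not met, non-parametric analyses will be undertaken to identify and locate the differences": Friedman with Wilcoxon inside groups, Kruskal–Wallis with Mann–Whitney across groups. HRV has a similar alternative (MANOVA, or Mann–Whitney and Friedman).

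The section names no normality test or threshold. It does not say whether scores, residuals or within-child differences are examined, or whether the check is made per measure or once for all three. On level and intervals it says "A significance level of 0.05 (5%) will be defined" and "all intervals constructed throughout the work will be 95% statistical confidence".

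Three other places matter:
- The Assessments for Primary Outcome section includes the coincident timing task.
- The Randomisation section defines the groups as the sequences A-S and S-A.
- The sample-size paragraph after the Figure 2 legend gives "The power was 0.80; the alpha was 0.05; and the effect size was 0.65 (Cohen's d") and "28 participants would be necessary (i.e., 14 per group").

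**The concern.** This is a stated decision rule, not a detail left for later. The outcome data select the method, and the two branches need not answer the same question.

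In a two-period crossover, the treatment effect is the within-child active-minus-sham difference, combined over both sequences so that any period effect cancels. ANOVA can carry that contrast, although the text does not say that it will. The rank branch is divided into within-group and between-group tests. If the groups are the two sequences, a between-group test on one period discards each child's own control. A within-group test uses only half the children and mixes the treatment effect with any period effect. The protocol itself expects all children to improve with VR practice, so a period effect is not far-fetched.

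At stake are the ability to detect an effect on these measures, and the clarity of a report in which three summaries of the same attempts may be analysed in different ways.

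**Working it through.** **Inputs from the protocol.** d = 0.65, alpha 0.05, 28 evaluable children (14 per sequence). Allowing for 20% withdrawal, 28/(1 − 0.20) = 35, and 36 are recruited (18 per sequence). Acquisition attempts per assessment: "with 20 repetitions for acquisition". The 28 serves here only to set group sizes. A crossover calculation returns 28 if the within-child correlation is 0.3, a value the protocol does not state. Whether 28 is right is a separate question.

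**1. Do the three measures land in different branches?** Assumptions not in the protocol: Shapiro–Wilk at 5%, applied per measure; between-child SD of bias 50 ms; median within-child SD 100 ms, varying between children with log-SD 0 to 0.7; each child's bias and spread equal in both periods. The table shows the share of simulated trials in which the three measures do not all fall in the same branch (normal attempt errors, no mean bias).

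| Log-SD | Raw scores, within groups, n = 14 / 18 per group | Within-child differences, n = 14 / 18 per group |
|---|---|---|
| 0 | 40% / 48% | 14% / 14% |
| 0.2 | 39% / 48% | 22% / 22% |
| 0.35 | 53% / 61% | 38% / 44% |
| 0.5 | 65% / 76% | 56% / 61% |
| 0.7 | 73% / 77% | 59% / 53% |

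Adding a mean bias of −50 ms and heavy-tailed attempt errors gives 40 raw-score settings. They span 39–79%, and 29 of the 40 lie between 50% and 74%. The differences span 14–61%. One joint check for all three measures gives 0%.

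The object of the check also changes which measures fail. With bias SD 60 ms, median SD 90 ms and log-SD 0.35, normality fails for constant / absolute / variable error as follows:
- raw scores: 9% / 31% / 42% at 14 per group and 10% / 41% / 52% at 18;
- within-child differences: 19% / 14% / 18% and 22% / 19% / 21%.

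The contrast between the signed and the zero-bounded measures is present in raw scores and absent in differences.

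**2. What does the rank branch cost?** Assumptions: normal data, 14 per sequence, two-sided 5%, no carryover or period effect, within-child correlation ρ of 0.3, 0.5 or 0.7.

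- *Combined within-child contrast, 28 children.* Standardised difference d_z = 0.65/√(2(1 − ρ)) = 0.549, 0.650, 0.839. Noncentrality d_z√28 = 2.91, 3.44, 4.44 on 26 degrees of freedom. Power 80%, 91%, 99%.
- *Mann–Whitney between sequences, period 1.* The t-test noncentrality is 0.65 × √(14/2) = 1.72, which gives 38%. The rank test gives about 34%, whatever ρ is.
- *Wilcoxon within one sequence, 14 children.* The t-test noncentrality is d_z√14 = 2.06, 2.43, 3.14. The rank test gives about 47%, 59%, 80% by simulation (46–80% over repeated runs).
- *Wilcoxon on all 28 within-child differences, for comparison.* 78%, 90%, 98% by simulation.

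The last line shows that ranking costs little. The loss comes from giving up the combined contrast.

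**3. Type I error.** In a two-group comparison, the two-stage rule rejected a true null in 4.7–5.7% of simulated trials, close to the nominal 5%.

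**The case against.** The strongest case against is that this is a common, pre-stated fallback. The Blinding section keeps the statistician blind to allocation until after the analysis, so the choice cannot be steered towards a result, and type I error stays near 5%. Both points stand.

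It is also true that the protocol specifies no particular check. Every splitting percentage is therefore conditional on a reading of the text, and none is a property of the plan as written. A reader might infer that the measures will usually be split because two of them are bounded at zero. That follows only if raw scores are checked per measure. With differences the contrast between measures vanishes, and with one joint check there is no splitting. Nor is the check close to a coin toss in general: under the raw-score assumptions only variable error comes near that.

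A reader might also infer that the rank branch breaks a promise of effect sizes and intervals. The documents do not support this. The interval sentence sets the level for whatever intervals are made, the ANOVA branch names no estimate either, and a separate analysis plan may supply both.

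Finally, the primary outcome covers several scales and tasks, so the rule does not govern the whole primary claim.

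What survives is that the data-driven switch is in the text, and that the tests named for its second branch fit a crossover poorly.

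**Conclusion.** The point holds in a limited form, and the plan should be tightened. The protocol lets the data choose the method for the timing errors without defining the check, and the named fallback does not combine both sequences into the crossover contrast if groups means A-S and S-A. Under the step 2 assumptions, that can lower power from 80–99% to about 34% (between sequences) or 46–80% (one sequence). If groups instead meant the active and sham conditions, a Mann–Whitney test would treat a child's two periods as independent, and the pairing would again go unused.

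Splitting of the three measures is possible rather than established: illustratively 50–74% in most raw-score settings, 14–61% on differences, none under a joint check. The harm is lost power and a method settled only after the data are seen. It is not false-positive inflation, and the documents do not show that effect sizes will go unreported.

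**What to change.** Before unblinding, state one main analysis for constant, absolute and variable error alike: a linear crossover analysis of within-child active-minus-sham differences that uses both sequences, reported as an estimate with a 95% confidence interval. Fix any transformation in advance, for example log for absolute and variable error and none for constant error. Name a rank test on the same within-child differences as a sensitivity analysis that is always reported, not as a replacement triggered by a normality check. Delete the conditional wording.

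The cost is a change of text, with no extra data or children. One small downside is that log-transformed measures are reported as ratios while constant error stays in milliseconds. The gain is therefore prespecification and use of the crossover contrast, not a common scale.

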### VR Task for Assessment

We will use two VR tasks to assess the participants' capacity and improvement with intervention. The tasks will be used as assessment at three points: initial assessment (D0); assessment after 5 sessions (D5); and final assessment (D11).

The assessment tasks are presented below:

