## Primary Outcome

To evaluate the effect of the combined therapy of virtual reality and tDCS in the upper-limb and trunk motor area on M1 (C1 or C2) of individuals with CP, and to check the possibility of generating motor gains in individuals with CP, we will observe the change from baseline motor values provided by different scales and VR tasks.

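### The primary motor outcome is change from baseline, analysed without a covariate, so the D0 scores already collected are used inefficiently; the cost is precision, and its size depends on a correlation the protocol does not give

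*Protocol article*

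**What the plan says.** The design is a two-sequence crossover (Overview of the Study Design): "A triple-blinded randomised controlled crossover trial with a 1:1 allocation ratio will be conducted". Each child receives active and sham stimulation, separated by a one-month washout that this section describes as sufficient.

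Under Primary Outcome, "we will observe the change from baseline motor values provided by different scales and VR tasks". The VR assessment tasks are given at three points (VR Task for Assessment): "initial assessment (D0); assessment after 5 sessions (D5); and final assessment (D11". Assessments for Primary Outcome gives the same three stages for the wider set of tests. The abstract places evaluations at baseline, during and after both active and sham tDCS, which I read as one D0 per period.

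Under Statistical Analysis, if parametric assumptions are met, "ANOVA will be performed to identify intra and inter-group differences", followed by Tukey tests. Otherwise Friedman and Wilcoxon tests are used within groups, and Kruskal-Wallis and Mann-Whitney tests between groups. No covariate or baseline-adjusted model is named anywhere. The visual, cognitive and other characterising assessments enter only through correlation tests with motor improvement, which do not adjust the active-sham comparison.

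**The concern.** Subtracting D0 forces its slope to be 1. In a crossover this can be expensive. The stable part of each child's ability already cancels when the child's two periods are compared, so subtracting two period baselines can add the noise of two more measurements and remove little. Estimating the slope from the data avoids that.

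The trial is small: 28 children are judged necessary and 36 are to be recruited. The effect sought is an increment of active over sham on top of a gain from VR practice that the Introduction expects in all children. An analysis with avoidable variance widens the interval for that increment and makes it easier to miss.

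**Working it through.** **Inputs from the protocol article.** From the sample-size paragraph below the Figure 2 caption: "The power was 0.80; the alpha was 0.05", "the effect size was 0.65" (Cohen's d), 28 children (14 per group) before withdrawals and 36 recruited. From Statistical Analysis: "A significance level of 0.05 (5%) will be defined".

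**Assumptions.** Alpha is two-sided (sidedness is not stated). d = 0.65 is the standardised change contrast (the article does not say whether it is paired or between groups). D0 and D11 have equal variance, as do their between-period differences. Each period has its own D0. The article gives no correlation, so a range is shown.

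**The plan's own figure.** With d = 0.65, 80% power and two-sided 5%, noncentral-t calculations give 39 per group for a two-sample test and 21 in total for a paired test. Neither is 28. That is a separate matter; 28 is used below simply as the planned evaluable number.

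**Variance ratio.** With unit variance and correlation r:
- change score: 2(1 − r)
- D11 alone: 1
- baseline-adjusted: 1 − r²
- change relative to adjusted: 2(1 − r)/(1 − r²) = 2/(1 + r)
- D11 alone relative to adjusted: 1/(1 − r²)

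For a single-period comparison between groups, r is the D0-D11 correlation. For the within-child contrast, r is the correlation between the between-period D0 difference and the between-period D11 difference.

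**Power for the within-child contrast, 28 children.** The noncentrality is 0.65 × √28 for change (26 df) and 0.65 × √28 × √(2/(1 + r)) for adjusted (25 df). Change scores give 91.1%.

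| r | Excess variance of change | Adjusted power |
|---|---|---|
| 0.3 | 2/1.3 − 1 = 54% | 98.4% |
| 0.5 | 2/1.5 − 1 = 33% | 96.8% |
| 0.7 | 2/1.7 − 1 = 18% | 94.8% |
| 0.8 | 2/1.8 − 1 = 11% | 93.6% |

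With 21 children and r = 0.5, power is 80.7% for change and 90.2% adjusted.

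**Relating the crossover r to ordinary correlations.** If w is the D0-D11 correlation within a period and b the correlation between any two measurements in different periods, then r = (w − b)/(1 − b). With w = 0.5:
- b = 0: r = 0.5, ratio 1.33
- b = 0.25: r = 0.33, ratio 1.50
- b = 0.5: r = 0, ratio 2.00

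Simulation with 28 children, which includes the cost of estimating the slope, gave ratios of 1.30, 1.45 and 1.97.

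**Carry-over.** Suppose a fraction k of the active increment d persists through period 2. It is then present in both the D0 and the D11 of period 2 in the active-first sequence.
- Change score: the persisting part cancels, so the expected estimate is d.
- Adjusted: the expected estimate is d × [1 − k(1 − r)/2].

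At r = 0.5 and k = 1 this is 0.65 × 0.75 = 0.49, an attenuation of 25%. In simulation the adjusted power fell to about 75%, against 91% for change scores. Break-even at r = 0.5 solves (1 − k/4) × √(4/3) = 1, so k = 0.54, roughly half the increment retained.

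**The case against.** **The remedy is not free.** This is the strongest objection, and it stands. The Introduction predicts retention at the 30-day follow-up, about the length of the washout. If the active increment persists, the period-2 D0 in the active-first sequence has itself been altered by treatment, and adjusting for it attenuates the estimate. A reader might infer that baseline adjustment can never do worse than change scores. In this crossover that holds only if the washout claim in Overview of the Study Design is correct.

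**One third is not a figure for this trial.** This also stands. A reader might take 33% as the loss, but 0.5 is an assumption. At r = 0.8 the excess is 11%, and in the within-child contrast r is not the ordinary D0-D11 correlation.

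**How D0 enters the tests is partly inferred.** The Primary Outcome section names change from baseline, but Statistical Analysis refers to the error measures themselves. That D0 is one of the levels compared by ANOVA is a fair reading of the within-group comparison, but it is not stated. If D11 values were compared without subtraction, the excess would be 1/(1 − r²) − 1: nothing at r = 0, 10% at 0.3 and 33% at 0.5.

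**Covariates are often left to the analysis plan.** This carries less weight. The article does not merely stay silent: it fixes the form of the outcome and names the tests, so adding a D0 covariate would change those statements.

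**The larger power gain is borrowed.** For a single-period comparison with 14 per group, power at r = 0.5 is 38% unadjusted and 48% adjusted. A reader might quote that gain, but the article does not commit to such a comparison, and the low starting power mainly reflects the group size.

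**Conclusion.** The point holds as one of efficiency. The protocol names change from baseline with covariate-free tests, and D0 could be used better at almost no cost. The excess variance of the change-score contrast is 11% to 54% for r between 0.8 and 0.3. For 28 children that means about 2 to 7 power points on a base of 91%. The figures rest on d = 0.65 being the standardised change contrast, two-sided 5%, equal variances, a D0 in each period and no carry-over.

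Nothing here shows bias: without carry-over both analyses estimate the same effect. Nor do the documents support a single loss figure or an unconditional preference for adjustment. The gain belongs to the crossover contrast only as far as the washout can be relied on.

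**What to change.** In Primary Outcome and Statistical Analysis:

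1. Make the D11 (and D5) motor score the outcome, and do not test D0 as an outcome level.
2. For the crossover contrast, regress each child's between-period D11 difference on sequence and on the between-period D0 difference. With the difference taken in period order, the sequence term carries the active-sham effect and the intercept the period effect.
3. For any single-period comparison between groups that is kept, use the same measure's D0 as the covariate.
4. State that the crossover version relies on the one-month washout being sufficient. Compare period-2 D0 between sequences, and keep the change-score contrast as a sensitivity analysis.
5. Confirm that a D0 assessment is made at the start of each period.

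If D0 is already measured in both periods, this changes wording only: no extra children or visits, and SPSS can fit the model. The price is one degree of freedom for the slope and the dependence on no carry-over described above. The change should be made before the allocation codes are opened.
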